### Eligibility Criteria

The following inclusion criteria were defined:
–chronic tic disorder or TS according to DSM-5–age ≥18 years–total tic score of the Yale Global Tic Severity Scale (YGTSS–TTS) >14 (for patients with TS and YGTSS–TTS >10 for patients with other chronic tic disorders)–CGI-S >4 at baseline–If patients receive additional medical or surgical treatment for tics and psychiatric comorbidities, they must be on a stable dose for at least 6 weeks before entering the study–fluency in German language–written informed consent.

Exclusion criteria for this study are:
–history of schizophrenia or pervasive developmental disorders–current diagnosis of substance abuse or dependence–primary comorbidities such as OCD, ADHD, depression, anxiety disorder, in need of therapy–history of behavioral treatment for tics (CBIT, HRT, ERP)–secondary tic disorders and other significant neurological and psychiatric diseases (such as schizophrenia, thought disorder)–no access to Internet or inability to operate a computer–participation in any interventional clinical study investigating drugs/medical devices 6 weeks prior to study enrollment.

These broad inclusion and exclusion criteria were based on the study by Wilhelm et al. (7), and guarantee that a representative group of TS treatment-seeking patients will be included, in particular, patients (1) with moderate or severe tics, (2) with simple or complex tics, (3) with or without comorbidities, (4) with or without additional drug treatment, (5) with short or long disease duration, and (6) of different age groups.

### Randomization

Potential bias will be minimized by randomized treatment allocation. The randomization list will be based on permuted blocks and is stratified by study site and pre-existing medication for the treatment of tics (yes/no). There will be a 1:1 randomization in four/five centers (for reasons explained above), and only in Hannover patients will be randomized 1:1:1 until 16 patients are randomized to face-to-face CBIT and 1:1 afterward. The randomization will be conducted centrally *via* web randomization. Patients will be given a sealed envelope by the investigator containing the access code for the therapy platform (or – only at the MHH center – information for face-to-face CBIT).

### Blinding

The study is observer blind. Although the patients will receive no information as to which treatment arm they are assigned to, it can be assumed that patients will find out. This will definitely be the case in the face-to-face CBIT treatment arm, but will most likely happen in the iCBIT – and placebo treatment arms as well, since all patients will be informed about the study objectives and the contents of the possible treatment arms. Thus, a genuine blinding of patients will not be possible. This represents a fundamental problem in all studies with psychotherapeutic interventions. However, much effort is being put into avoiding the unblinding of study physicians:
The examiners involved in the study will only carry out assessments. Apart from this, they will not be responsible for the treatment of patients during the study period and will not answer questions related to the therapy.Patients will be instructed in writing, neither to talk nor to ask questions about the contents of the therapy during the study visits. In addition, patients will be explicitly asked by the examiner at the beginning of each visit (telephone and personal study visits), not to talk about the contents of their therapy. Technical as well as content-related assistance related to the online platforms will be provided *via* a central hotline located in Hanover through a study staff member who will not be involved in assessments.Despite these precautions, a blinding of the evaluating study physicians cannot be guaranteed to 100%. If an investigator will be unblinded by a patient, this will be documented directly at the respective visit. Whenever possible, the patient will be reassessed by an alternative unblinded investigator at this visit (if unblinding happened before the completion of this study visit) and at all following visits.The therapist, who will treat patients with face-to-face CBIT within this study will not be involved in clinical assessments.The recording and scoring of videos for tic assessment will not take place in the same center (videos will be analyzed centrally at the MHH) and only after termination of the study, thus blinding of the evaluating physician is guaranteed.

### Compliance

In order to ensure that the patients will take active part in the Internet-based intervention, several automated checkups are integrated into the online platform for two purposes: first, it allows to organize and motivate the patients with regard to their sessions (missed sessions, time in session, active reminder, and more). Second, a direct quantification of the compliance is possible after study completion and compliance can be analyzed statistically.

To all patients randomized to the placebo platform, an (open, uncontrolled) participation in the iCBIT therapy will be offered after study completion. However, this will only be possible for those patients in the face-to-face CBIT and the placebo treatment arms, who have been compliant before and completed the randomized treatment.

### Internet-Delivered CBIT

Comprehensive Behavioral Intervention for Tics can be regarded as an “extension” of HRT developed for the treatment of patients with tics including psychoeducation, tic-awareness training (including the awareness of premonitory urges preceding the occurrence of the tics), CRT, relaxation training, and functional analysis to identify events and situations that influence tic severity in order to develop coping strategies to manage these situations. HRT, the primary component of CBIT, is based on the premise that tics are maintained by response chaining, lack of awareness of their occurrence, excessive practice, social reinforcement, and tolerance of the tics (19). The core element of HRT, in turn, is CRT that aims to introduce a voluntarily performed non-tic movement that is physically incompatible with the performance of the tic. Thus, the competing response encourages the subject to respond to the urge by performing a movement competing with the tic. Over time, performance of the competing response breaks the cycle between the premonitory urge and the relief following the tic.

The iCBIT online platform is being created by the authors ([name], [name], [name], and [name]) and in particular by [name], who is well experienced in all aspects of TS, and [name], who is an experienced and well-trained psychotherapist for CBIT in adults. It is following the manual for face-to-face CBIT by Woods (20) with respect to both, number and content of treatment sessions, distribution of CBIT elements to particular treatment sessions, and duration of treatment. Thus, the only difference between this conventional and well established form of CBIT and iCBIT will be the route of delivery, on the one hand *via* face-to-face and on the other hand *via* Internet. Only very few adaptations have been inevitable due to Internet-delivery such as more extensive psychoeducation, description of CBIT at great length and inclusion of additional contents. For example, for better illustration, videos will be included where patients as well as an expert clinician ([name]) talk about their own experience with both CBIT and TS as well as general aspects of TS and contents of CBIT. Additional content will be offered in form of a FAQ section, which is meant to provide answers to most frequent questions that might arise over the course of the program. Comparable to the Woods’ manual for face-to-face CBIT, other resources are provided including information about the TS, working materials such as “Personal Tic Sheet,” “The Tic Symptom Hierarchy Tracker,” “Functional Assessment Form” (to help patients identify situations that deteriorate their tics in order to develop specific function-based interventions), “Tic Hassle Form,” a list of possible competing responses for different tics, and a reward program. Working sheets can either be used online or can be printed out for use in paper form. A part of the working materials can alternatively be used *via* smartphone app.

In line with the CBIT manual provided by Woods (20), iCBIT will consist of eight sessions of which the first two session will take 90 min, while the other six sessions will take 60 min. The first six sessions will be weekly and the last two sessions will be biweekly, totaling to an overall treatment duration of 10 weeks. However, iCBIT will allow patients more time flexibility than conventional face-to-face CBIT.

### Placebo: Online Psychoeducation

The control group will consist of psychoeducation only. It will match the iCBIT group in terms of the number and duration of sessions (eight Internet-delivered sessions over a period of 10 weeks). Patients in the control group will receive no elements of CBIT. Psychoeducation will include additional disorder-specific information. A comparable design has been chosen in available large RCTs using face-to-face CBIT (6, 7). Due to the well-known disadvantages of waiting list designs, we decided against using it in our study (21).

### Face-to-Face CBIT

This additional treatment arm will only be offered in Hanover. The face-to-face CBIT therapy will follow the CBIT manual by Woods et al. (22). In addition, each face-to-face session will correspond exactly to the iCBIT sessions: treatment will thus consist of eight sessions of which the first two sessions will last 90 min and the remaining six sessions 60 min (total of 10 weeks).

### Booster Sessions

In the period of time from the end of active treatment until the last follow-up visit (see below), patients in all treatment arms will get the option of receiving booster sessions to refresh the therapy. There will be no limitation in terms of number, scope, and duration of these additional sessions in the Internet-based treatment arms. In these sessions, patients will have access to information earlier provided in the eight sessions of their treatment module. However, no new information or contents will be offered. In the face-to-face CBIT group, up to two booster sessions will be possible in terms of face-to-face CBIT sessions with the therapist [comparable to the CBIT manual by Woods et al. (22) and recent studies (7)]. The duration of these sessions will be 60 min each.

### Online Platform: Minddistrict

The technical implementation of the Internet-based treatment is being set in place in cooperation with the Minddistrict company. All treatment-related contents for the online modules are being developed by the research team at the MHH. In the final stage of development, the platform will be reviewed by the authors of the original CBIT manual [name] and [name] (who is a German native speaker). Prior to study begin, the platform will be additionally pilot tested by a small group of patients with tic disorders to verify its practicability and usability. Feedback will be used for further optimization of the platform before study launch.

### Outcome Measures

The primary outcome measure will be the YGTSS–TTS (23) 1 week after end of treatment. This has also been used in studies demonstrating efficacy of face-to-face CBIT (6, 7). Tic severity will further be assessed *via* several secondary outcome measurements using (i) the YGTSS–TTS 3 and 6 months after end of treatment, (ii) the Modified Rush Video-Based Tic Rating Scale (MRVS) (24), and (iii) the Adult Tic Questionnaire (ATQ), a tic self-rating scale, which is parallel in format and content to the Parent Tic Questionnaire (25).

The following further secondary outcome measures will be included: the Premonitory Urge of Tics Scale (PUTS) (26), Beck Depression Inventory (BDI-II) (27), Conners’ Adult ADHD Rating Scale (CAARS) (28), Yale-Brown Obsessive-Compulsive Scale (Y-BOCS) (29, 30), Beck Anxiety Inventory (BAI) (31), Gilles de la Tourette Syndrome-Quality of Life Scale (GTS-QoL) (32). In addition, the Clinical Global Impression – Severity Score (CGI-S) and the Clinical Global Impression – Improvement Score (CGI-I) will be used to measure overall severity of disease and improvement at follow-up. An adopted version of the Working Alliance Inventory-Short Revised (WAI-SR) will be applied to assess the therapeutic alliance (33).

### Schedule of Assessments

All clinical assessments will be performed at screening, baseline, week 5 (during treatment), week 11 (1 week after end of treatment), and 3 and 6 months after end of treatment. Follow-up assessments at 3 and 6 months after the end of treatment will provide estimates of the durability of treatment effect. Thus, time points of assessment in this study are comparable to those in the study by Wilhelm et al. (7), which recently demonstrated that face-to-face CBIT is an effective and safe intervention in adults with TS. Randomization will be performed at the baseline visit. Screening and baseline visits should not be more than 4 weeks apart, otherwise the patient will have to be rescreened. A detailed assessment schedule is provided on Table 2. At week 17 and 29 (1.5 and 4.5 months after the end of treatment), telephone visits will take place. These additional visits serve the purpose of improving compliance in order to keep the drop-out rate as low as possible. During these telephone visits there will be no further testing.

**Table 2 T2:** **Assessment schedule**.

Study period	Screening	Baseline	Treatment: (a) iCBIT, (b) placebo, (c) Face-to-face CBIT								Follow-up visits/booster-treatment^a^				
**Visit**	1	1					2				3		4		5
**Week**	−4 −0	0	1	2	3	4	5	6	8	10	11	17	23	29	35
**Treatment-session**			1	2	3	4	5	6	7	8	Frequency individual, for face-to-face CBIT: max = 2				

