**Adverse events**															
Open question							X				X		X		X

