**Therapeutic alliance**															
WAI-SR							X				X		X		X

*YGTSS, Yale Global Tic Severity Scale; MRVS, Modified Rush Video-Based Tic Rating Scale; ATQ, Adult Tic Questionnaire; CGI-S, Clinical Global Impression–Severity Score; CGI-I, Clinical Global Impression-Improvement Score; PUTS, Premonitory Urge of Tics Scale; GTS-QoL, Gilles de la Tourette Syndrome-Quality of Life Scale; BDI-II, Beck Depression Inventory; ADHD, Attention Deficit Hyperactivity Disorder; CAARS, Conner’s Adult ADHD Rating Scale; OCD, Obsessive-Compulsive Disorder; Y-BOCS, Yale-Brown Obsessive-Compulsive Scale; BAI, Beck Anxiety Inventory, WAI-SR, Working Alliance Inventory-Short Revised*.

*^a^Booster-sessions: booster-session are optional. Frequency, scope, and number will vary individually in the iCBIT and placebo groups, in the face-to -face CBIT group up to two booster sessions a 60-min between week 11 and 35 are possible*.

*^b^Compliance: the compliance of patients in all treatment arms will be assessed during the telephone and in person visits. In the face-to-face CBIT treatment, arm compliance will also be determined via regular and full participation in the therapy sessions. In the iCBIT and placebo groups, the participation in the therapy session will be determined automatically by the online platform by collecting information on when, how long and where the patients were logged in*.

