### Safety

For this study, no safety issues have been identified. Adverse events and incidents will be documented *via* open questions and will be analyzed descriptively. Patients can contact the recruiting center at any time. If required, however, unblinding will be possible at any time.

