## Discussion

### Clinical Implications

This is the first study examining the efficacy and safety of a fully self-sufficient Internet-delivered behavioral therapy using CBIT for adult patients with chronic tic disorders that does not require the supervision of a therapist (ONLINE-TICS). We will carry out a large multicenter, RCT in five different German TS centers to compare the efficacy of iCBIT [an online therapy, which follows closely the CBIT manual by Woods (20)] to (1) an online placebo – containing only psychoeducation – and to (2) a conventional and well-established face-to-face CBIT treatment. The inclusion of both an online-delivered placebo intervention and face-to-face CBIT gives us the unique possibility to investigate not only the superiority of iCBIT over placebo but also the non-inferiority compared to face-to-face CBIT.

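### The week 17 and 29 telephone visits omit the adverse-event question, so the solicited recall window doubles to 12 weeks in follow-up

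*Protocol article*

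**What the plan says.** All references are to the protocol article.

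- **Calls.** The Schedule of Assessments states: "At week 17 and 29 (1.5 and 4.5 months after the end of treatment), telephone visits will take place". Their purpose follows: "These additional visits serve the purpose of improving compliance in order to keep the drop-out rate as low as possible". It then adds: "During these telephone visits there will be no further testing".
- **Compliance.** Table 2 marks the compliance question at both calls, and its footnote b confirms that "the compliance of patients in all treatment arms will be assessed during the telephone and in person visits".
- **Adverse events.** The only adverse-event row in Table 2, "Open question", is marked at weeks 5, 11, 23 and 35 and is blank at weeks 17 and 29. Under Safety: "Adverse events and incidents will be documented *via* open questions and will be analyzed descriptively". The same section says that no safety issue has been identified and that patients may contact the recruiting centre whenever they wish.
- **Boosters.** Under Booster Sessions, optional access runs from the end of active treatment to the last follow-up visit. For the online arms: "There will be no limitation in terms of number, scope, and duration of these additional sessions in the Internet-based treatment arms". The material repeats the eight sessions and adds nothing new.
- **Safety as an aim.** Under Clinical Implications: "This is the first study examining the efficacy and safety of a fully self-sufficient Internet-delivered behavioral therapy".

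**The concern.** The trial presents itself as a study of safety as well as efficacy, and open questioning is the only method of collecting adverse events that it describes. An open question without prompts depends on what the patient remembers. Recall is asked over roughly twice as long a period after week 11 as before it, at the stage when scheduled contact is sparser and patients may still be using the modules. A study contact already falls in the middle of each long window, with a compliance question scheduled and no adverse-event question.

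At stake is the completeness and dating of mild or short-lived events in the descriptive safety summary for follow-up. Efficacy is not at stake.

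**Working it through.** No sample-size or power formula bears on this point. The check reads the marks in Table 2 against its week header and takes differences.

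**Inputs (Table 2)**

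| Row | Weeks marked |
|---|---|
| Adverse-event open question | 5, 11, 23, 35 |
| Phone visits | 17, 29 |
| Asking for compliance | 1, 2, 3, 4, 5, 6, 8, 10, 11, 17, 23, 29, 35 |

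**Step 1: windows as planned.** Window = week of this question minus week of the previous one, starting at baseline (week 0).

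- 5 − 0 = 5
- 11 − 5 = 6
- 23 − 11 = 12
- 35 − 23 = 12

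**Step 2: share of observation time in the long windows.** (12 + 12) / 35 = 24/35 = 69%, covered by two questions.

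**Step 3: position of the calls.** Week 17 is 17 − 11 = 6 weeks into the first long window, and week 29 is 29 − 23 = 6 weeks into the second. Each call sits exactly at the midpoint.

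**Step 4: windows if the calls carried the question.**

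- 5 − 0 = 5
- 11 − 5 = 6
- 17 − 11 = 6
- 23 − 17 = 6
- 29 − 23 = 6
- 35 − 29 = 6

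The longest window falls from 12 to 6 weeks and matches the period up to week 11.

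**Step 5: what this means for recall.** If events are assumed to be spread evenly within a window, the average delay from event to question is half the window: 12/2 = 6 weeks as planned, and 6/2 = 3 weeks with the calls used.

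**Step 6: volume.** Two extra questions for at most 160 patients give at most 2 × 160 = 320 additional questions, fewer after drop-out.

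The number of events that would be recovered cannot be calculated, because the article gives neither an event rate nor a rate of recall loss.

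**The case against.** The strongest reply is that nothing here is wrong. Text and table agree, the calls have a stated retention purpose, and adverse events are asked at every in-person visit after baseline. The sentence about no further testing concerns assessments and would not by itself prevent a caller from recording an event that a patient mentions. Patients have an open line to their centre, no safety issue is expected, and boosters are optional repeats of known content. The depression, anxiety, obsessive-compulsive and quality-of-life scales and the global impression ratings are repeated at weeks 23 and 35, so sustained worsening has structured capture.

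Most of this stands. There is no contradiction, and the gap concerns solicited collection only. What remains is that reporting on one's own initiative, and scales taken at week 23 or 35, do not replace a scheduled question for events that come and go in between. Nor is this a detail lost in condensing the protocol: the article gives the full visit grid and leaves these two cells blank.

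A reader might infer more, and the documents do not support it:

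- **That follow-up event counts will be too low.** Under-recall is plausible, but no figure in the article allows its size to be stated, and no comparison of event rates between treatment and follow-up is described.
- **That detection differs between arms.** iCBIT and placebo share the same adverse-event schedule and booster rules. The face-to-face arm (16 patients) may have up to two therapist boosters, but nothing says that the therapist collects adverse events, and the Blinding section keeps the therapist out of clinical assessments.
- **That the calls should move to the central hotline to protect blinding.** The same open question is already asked at the in-person visits under the instruction not to discuss therapy content. The hotline member helps with platform content and so may know the arm.

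**Conclusion.** The concern holds as a modest weakness in a fixed schedule. Solicited recall windows are 5, 6, 12 and 12 weeks. The two long ones cover 69% of the time after baseline, and each contains a call at which the adverse-event question is not scheduled. The consequence is a risk that mild or passing events in follow-up are forgotten or misdated; collection itself is not missing.

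This rests on reading the blank cells in Table 2 as meaning that the question is not asked at the calls, which the text supports, and on the general premise that unprompted recall is weaker over 12 weeks than over 6. The primary endpoint at week 11 and the efficacy analyses are untouched, and the iCBIT versus placebo comparison has the same ascertainment schedule in both arms. It is an inexpensive improvement and no reason to doubt the trial's main conclusion.

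**What to change.** - **Table 2:** mark the adverse-event open question at weeks 17 and 29.
- **Schedule of Assessments:** replace the statement about the telephone visits with one saying that no psychometric testing is done but adverse events are asked.
- **Callers and blinding:** leave the current callers in place. Keep the Blinding section's instruction that patients should not discuss therapy content, as at the in-person visits.

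The cost is a few minutes per call and slightly more adverse-event documentation. No visit, scale or analysis is added, because the calls are already scheduled for all arms and the existing descriptive summary can take the extra reports.
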